### Data collection

Here we describe data collection for intervention group and both control groups. Demographic data will be collected at baseline (T0). Quantitative outcome data (health status, subjective wellbeing, social integration and economic status) will be collected at baseline (T0), 12 months (T1) and 24 months (T2) from intervention and control group participants. The 12-month intervals are designed to mitigate seasonal effects for any given cluster. The evaluation timeline is shown in Fig. 6.

**Fig. 6 Fig6:**
[figure not shown]
Evaluation Timeline •We have chosen not to specify when baseline data collection will begin due to uncertainty over COVID-related local travel restrictions. •The baseline data collection will last approx. Twenty-four to Twenty-six weeks for all groups. •Quantitative data collection for control and intervention groups will begin together at baseline, and repeat at 12 and 24 months. Quantitative data collection will be staggered, such that for each cluster, data will be collected exactly 12 months apart to avoid seasonal effects. •Qualitative data collection for both the intervention and control groups will also take place 12 months apart, between quantitative data collection periods. •Qualitative data collection from *broader community, e.g. facilitators, community leaders/village chief, healthcare professionals, will follow initial analysis of intervention group interviews, as these will suggest the types of people in the community who are likely to have a mediating effect on the intervention.

Process evaluation data from qualitative observations for intervention group and control group members will be collected between 7 and 9 and 19–21 months after enrolment (Q3 in Fig. 6). Process evaluation observations from the broader local community will occur between 10 and 12 and 22–24 months after initial enrolment. It is envisaged that group members’ comments will help to determine the most influential community members for interview (refer to eligibility criteria above).

### Demographic data

Demographic data (age and sex), and concurrent diseases will be collected for all consenting intervention and control group participants. Clinical data (e.g., number and size of ulcers) will be collected for people affected by leprosy only.

### Quantitative data

*Health, social and economic wellbeing (all participants)*

The four generic outcome measures are:
i.Generic health status (quality of life). Data will be collected using a standardised instrument, the EQ-5D-3L [12]. A country specific digital version will be used. As far as we are aware, there is no valuation tariff in the Nepalese population, although this may change by the time that the analysis starts. Therefore, we propose not to pre-specify the tariff but instead select the tariff at a later date. We note that tariffs are currently available for nearby countries including Sri Lanka [13] and China [14, 15].ii.Subjective wellbeing data. Data will be collected using a standardised five question instrument [16, 17] designed to capture evaluations of the participant’s level of life satisfaction, an evaluation of personal meaning and happiness, and their affective state.iii.Social integration. Data will be collected using the validated participation scale (p-scale) [18] which has been used in rehabilitation, stigma reduction and social integration programmes in low- and middle-income countries (LMICs). A Nepali language version is available.iv.Economic status will be measured by examining total household consumption. A consumption questionnaire has been derived from Sections 2, 5, 6 and 7 of the Nepal: Living Standards Survey (NLSS: 2011/12) [19]; see Additional File 1. The NLSS is a multi-topic household survey conducted by the Central Bureau of Statistics (CBS) of the Government of Nepal in conjunction with the World Bank which in turn is part of the Living Standards Measurement Surveys (LSMS) conducted by the World Bank. We have chosen to measure consumption rather than wealth or income for the following reasons. 1) Measuring income in LMICs is affected by fluctuations due to the informal nature of work and seasonal activity [20], while consumption is more stable over time [20, 21]. Asset (wealth) indices may be more stable [22] but are likely insensitive to change over the short-term observation period of this study.2.*Clinical Data (people affected by leprosy in intervention group and control group 2)*

Clinical data will be obtained from people affected by leprosy only. Limbs and eyes will be inspected by a researcher in Nepal, and their condition described using a standard form resident on the electronic tablet (see Additional File 2) with information on anaesthesia, ulcers and any visible impairments using the World Health Organisation (WHO) disability grading system [23]. The clinical appearance of any ulcer (e.g. any residual exudate) will be recorded [24, 25].

Ulcer metrics will be based on standardised photographs taken during dressing changes [26]. The measurements will use a photograph taken using the in-built camera in the tablet devices (Samsung Galaxy Tab S6). The photograph will be taken perpendicular to the ulcer. For calibration purposes, a 3 cm size clean paper ruler with date and participant’s identification number will be placed in the photograph frame above or below the ulcer but at the level of the skin. Each photograph will be assessed twice. First, the ulcers will be assessed using the PictZar™ Digital Planimetry Software [17] with an electronic PUSH Tool (National Pressure Injury Advisory Panel (NPIAP) at https://npiap.com/page/PUSHTool) by an independent research fellow in Kathmandu who will be aware of their order in the study timeline. The observer will delineate an area of interest by manually ‘painting’ the ulcer area with colour using a computer mouse. The software will then calculate the ulcer dimensions based on this profile. Second, the photographs will be assessed using the same tool by a research fellow at the University of Birmingham who will be blind to data collection time point. This will ensure that the main outcomes are assessed blind to intervention status and will be done at study end. The total area of all ulcers will be calculated and used as the ‘ulcer area’ metric in the analysis.

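### The calibration ruler puts the date and participant ID inside every ulcer photograph and no masking step is described, so the Birmingham reader's blinding to time point is not secured as described

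*Protocol article*

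**What the plan says.** The procedure is in the clinical data part of the Quantitative data section of the protocol article. For calibration, "a 3 cm size clean paper ruler with date and participant’s identification number will be placed in the photograph frame", next to the ulcer at skin level.

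The article then says "Each photograph will be assessed twice". The first reading is made "by an independent research fellow in Kathmandu who will be aware of their order in the study timeline". The second uses the same tool and is made "by a research fellow at the University of Birmingham who will be blind to data collection time point". The article concludes: "This will ensure that the main outcomes are assessed blind to intervention status and will be done at study end". In each reading the observer colours in the ulcer by hand with a mouse, and the software computes dimensions from that outline. The areas of all ulcers are summed to give the ulcer-area metric.

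On timing, the Data collection section says the four generic outcomes "will be collected at baseline (T0), 12 months (T1) and 24 months (T2) from intervention and control group participants". The Fig. 6 legend adds that "The baseline data collection will last approx. Twenty-four to Twenty-six weeks for all groups" and that each cluster's quantitative rounds are a fixed 12 months apart.

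**The concern.** The second reading is the article's protection against a reader who expects improvement and outlines later ulcers more tightly. The first reading offers none, because that reader openly knows the order. Yet the image passed to the second reader is captured with the one fact that reader must not have written in the frame, next to an ID that links all images of one person.

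This matters more here than in a concurrently controlled comparison. The second hypothesis under Aim of the evaluation compares ulcer prevalence and severity after the intervention with before. People affected by leprosy cannot enter control group 1. Control group 2 can supply clinical data, but the Discussion expects it to be too small for a precise concurrent comparison and accepts that the ulcer analysis will rest mainly on before versus after. Time point is therefore the contrast under test. Any drift in tracing that follows time point would look like healing, and there would be little concurrent data to separate the two.

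**Working it through.** The plan gives no figure to reproduce. The check has three steps.

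**1. Do the same images reach the reader said to be blind?** The text gives one set of photographs, taken with the dated and numbered ruler, and says each is assessed twice. No second, unlabelled set is mentioned, and no processing between the readings is described. The article does not say that the Birmingham reader sees the label, nor how it is kept from view.

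**2. Would a visible date reveal the time point?** Inputs: a baseline window of 24 to 26 weeks (Fig. 6 legend), and rounds 12 months apart within each cluster (Fig. 6 legend), taken as 52 weeks. With window length w, round k (k = 0, 1, 2) covers weeks 52k to 52k + w.

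| Round | w = 24 | w = 26 |
|---|---|---|
| T0 | 0–24 | 0–26 |
| T1 | 52–76 | 52–78 |
| T2 | 104–128 | 104–130 |

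The gap between rounds is 52 − w: 52 − 24 = 28 weeks, or 52 − 26 = 26 weeks. Rounds would overlap only if w exceeded 52 weeks, which is twice the longer planned window. On the stated calendar, every visible date therefore maps to exactly one round. Within one participant, dates and ID give the order even without knowledge of the study calendar. Because the second reading is done at study end, all rounds are available to the reader together.

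Assumption: ulcer photographs follow the T0/T1/T2 schedule. The Data collection section names only the four generic outcomes for those times. The Fig. 6 legend refers to quantitative data collection in general.

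**3. How would a tracing bias enter the result?** Let A be the true area, unchanged over time, and let follow-up ulcers be traced smaller by a fraction b. The measured ratio of follow-up to baseline is (1 − b)A / A = 1 − b, so the apparent fall in area equals b. The documents give no value for b and no expected ulcer effect to set it against, so this shows the route of the bias and not its size.

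**The case against.** The strongest reply is that the article states plainly that the Birmingham reader will be blind. A date present when the photograph is taken need not be present when it is read. The ruler is needed only for scale, so the writing on it can be covered or cropped without losing calibration. Image handling of this kind may sit in a full protocol or working instruction that is not shown.

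Much of this stands. A reader might infer that blinding is impossible, or that neither reading is blind. The documents do not support that: one reading is declared unblinded and the other blind, and masking remains feasible up to study end. What survives is narrower. The article goes into detail on the tablet model, ruler length and placement, software and tracing method, and it asserts that blinding is ensured. The one capture detail that bears on blinding works against that assertion and is left unreconciled.

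Three other stronger readings also go too far:

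- That the article falsely claims blinding for the four generic outcomes. The sentence about main outcomes directly follows the Birmingham reading, in the ulcer paragraph, and most naturally refers to that reading. The wording is loose, and intervention status is the wrong term for a before-after contrast, but this is an edit.
- That the source of the ulcer-area value is unknown. The Birmingham reading is the natural candidate, and naming it formally is often left to an analysis plan. It is still worth stating.
- That the bias has a known size. A figure such as 5% to 20% would be pure assumption. The Discussion also expects a larger effect on ulcers than on economic outcomes, and tracing bias acts on area, not on whether an ulcer is present.

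**Conclusion.** The concern holds in limited form. Date and participant ID are in the frame of the photographs that go to the reader described as blind to time point, and no masking step is described. The blinding is therefore not secured as described and is undercut by the dated label. If photographs follow the T0/T1/T2 schedule and the label stays visible, the date identifies the round for every image, with 26 to 28 weeks between rounds. This affects the main safeguard for a hand-traced outcome tested mainly before versus after. Whether the label is in fact hidden from the Birmingham reader, and how large any tracing bias would be, cannot be settled from the documents.

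**What to change.** 1. Put only the scale and a random image code in the frame, and hold the key linking code to date and ID in REDCap. If dated rulers must stay, or dated images already exist, crop or mask date and ID and strip the file metadata before export to Birmingham.
2. Give the Birmingham reader all images in random order across participants and time points.
3. State that this masked reading supplies the ulcer-area value for analysis and that the Kathmandu reading serves reliability.
4. Reword the blinding claim so that it covers only ulcer area, read blind to time point.

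The cost is a new label or a masking step in the image export, custody of the key, and a few sentences of text. No extra readers, visits or participants are needed. Because the Birmingham reading takes place at study end, masking can be applied even to photographs already taken.

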### Aim of the evaluation

The aim of the SHERPA evaluation is to determine whether the IMPACT intervention achieves its aims to improve health and wellbeing, social functioning and economic status. We hypothesise that:
Participants who receive the IMPACT intervention will experience greater improvement over time in the four universal outcome measures (generic health, subjective wellbeing, social participation and economic status) than people in control group 1.People affected by leprosy will experience a lower prevalence and severity of ulcers after the intervention than before.

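### The blind photographic reading cannot blind ulcer presence, so ulcer prevalence and the zero areas of people with no photograph rest on field inspection with no stated blinding

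*Protocol article*

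**What the plan says.** The ulcer hypothesis, in Aim of the evaluation, has two parts: "People affected by leprosy will experience a lower prevalence and severity of ulcers after the intervention than before".

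The clinical part of Quantitative data sets out how the ulcer data arise:

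- **Detection.** "Limbs and eyes will be inspected by a researcher in Nepal, and their condition described using a standard form resident on the electronic tablet". The form covers anaesthesia, ulcers and visible impairments.
- **Photographs.** "Ulcer metrics will be based on standardised photographs taken during dressing changes", and "The photograph will be taken perpendicular to the ulcer". A paper ruler bearing the date and the participant's identification number lies in the frame.
- **First reading.** A research fellow in Kathmandu measures the photographs, and is someone "who will be aware of their order in the study timeline".
- **Second reading.** A research fellow in Birmingham, who is not told the time point, measures the same photographs with the same tool. Of this the article says: "This will ensure that the main outcomes are assessed blind to intervention status and will be done at study end".
- **Metric.** Areas are summed over all of a person's ulcers.

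The Discussion expects the ulcer analysis to rest on a before-after comparison. People affected by leprosy are excluded from control group 1, and few are expected in control group 2.

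**The concern.** A blind reading protects only what the blinded person decides. Here that person measures the lesions that reach them as photographs. Whether a lesion counts as an ulcer at all is decided beforehand, face to face, by someone who would know whether the visit is baseline, 12 months or 24 months.

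In a before-after comparison the visit is the exposure. An inspector slightly readier at follow-up to call a lesion healed, or to call it callus or a fissure, would lower prevalence. The same call would turn a positive area into a zero. On the procedure as described, neither change could be seen or corrected in Birmingham. The sentence on blinding would then reassure readers about the one bias that the blind step does not reach.

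The Discussion defends the lack of contemporaneous controls for ulcers on two grounds: a larger expected effect, and less risk of a temporal trend. Neither concerns a drift in how lesions are classified.

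**Working it through.** The article states no ulcer prevalence, ulcer effect size or ulcer precision, so there is no figure to reproduce. The approximate 10% in Power calculation and sample size is for expenditure, wellbeing and health status. The check is to trace each ulcer quantity to the person who determines it.

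| Quantity | Determined by | Blind to visit? |
|---|---|---|
| Ulcer present or absent (prevalence) | Field inspection | No blinding stated |
| Zero area, no photograph | Field inspection | No blinding stated |
| Area of a photographed ulcer, first reading | Kathmandu fellow | No, by statement |
| Area of a photographed ulcer, second reading | Birmingham fellow | Yes, by statement, provided the date on the ruler is masked |
| Zero area, lesion photographed but read as closed | Birmingham fellow | Yes, same proviso |

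Only the last two rows support the blinding sentence. The article does not mention masking the date, and does not say which of the two readings enters the analysis.

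**How many values rest on inspection alone (illustration).** Study design gives 18 × 20 = 360 intervention members. Table 1 says about half are affected by leprosy, so n ≈ 360 × 0.5 = 180. With prevalence p (assumed), the number with no photograph at a visit is 180 × (1 − p):

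- p = 10%: 162
- p = 20%: 144
- p = 30%: 126
- p = 40%: 108

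**What a small shift in classification would do (illustration).** Suppose there is no true change and follow-up inspection records a fraction s of the ulcers that baseline inspection would have recorded. Apparent prevalence is p × s, a relative fall of 1 − s. At p = 30%, 180 × 0.30 = 54 people have an ulcer. With s = 0.95, 0.90 and 0.80, the number missed is 2.7, 5.4 and 10.8.

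**How that compares with sampling error (illustration).** Take a paired change with within-person correlation ρ = 0.5 (assumed) and independent people:

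SE = √(2p(1 − p)(1 − ρ)/n) = √(0.21/180) = 0.034

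The chance that a 95% interval shows benefit is 1 − Φ(1.96 − shift/SE), against 2.5% with no shift.

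- Shift 0.03 (10% of ulcers missed): 14%
- Shift 0.06 (20% missed): 42%

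With p from 20% to 40% and ρ from 0.3 to 0.7, the 10% case runs from 8% to 29%. Clustering and dropout are ignored. Positive intra-cluster correlation in change, or dropout, would enlarge the SE and lower these chances, but would leave the bias in place.

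**The case against.** The case on the other side has several parts.

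- **Inference from silence.** The article does not call the inspector unblinded, nor say that healed or doubtful sites go unphotographed. The clinical form is in Additional File 2, which is not shown and could require more photographs. This stands as a caveat. But the article describes photographs only of ulcers, and an inspector attending in person a year apart can hardly be unaware of the visit. The assurance about blinding is the article's own, and the procedure it describes does not deliver it.
- **A common field design.** In-person detection followed by blinded measurement is usual, and the article says the evaluation team had no part in developing the intervention. That lessens the motive for biased calls without removing the problem. Detection could also improve with practice, which would bias against benefit, so the direction is not known.
- **The expected effect is large.** The Discussion expects a much larger effect on ulcers than on economic outcomes. It gives no size, so a classification shift cannot be set against it.

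Three stronger readings are tempting and are not supported:

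- A reader might infer that every zero area is unblinded. It is not: a photographed lesion that Birmingham reads as closed gives a blinded zero.
- A reader might infer that the blinding sentence is false for the four generic outcomes too, since they come from questionnaires. The sentence belongs to the clinical data and refers to the photographic reading. Its natural meaning is the ulcer metrics, so the loose phrase is at most ambiguous.
- A reader might take 14% or 42% as this study's false-positive rate. Prevalence, correlation and miscall rates are all assumed, clustering is ignored, and the planned analysis is Bayesian with no such decision rule for ulcers.

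**Conclusion.** The point holds in a limited form. The blind reading can protect the area of photographed ulcers, provided the date is masked and that reading is the one analysed. It cannot protect ulcer presence, and so does not protect the prevalence part of the ulcer hypothesis or the zero area of a person with no photograph. Because the ulcer comparison is mainly before-after, this is where knowledge of the visit matters most.

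The conclusion rests on two readings of the article: that photographs are taken only of lesions identified as ulcers, and that the inspector knows the visit. The size and direction of any bias cannot be derived from the documents; the figures above only show that a modest shift could matter. The plan should be changed, because an analysis plan cannot later recover photographs that were not taken.

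**What to change.** In the clinical part of Quantitative data:

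1. At 12 and 24 months, photograph every site with an ulcer recorded at an earlier visit, as well as every current ulcer or doubtful lesion, whether or not the inspector calls it healed. Photograph doubtful lesions at baseline too, so that the visits are comparable.
2. Mask the date on the ruler before the Birmingham reading.
3. Have the Birmingham reader judge ulcer present or absent as well as area, and name that reading as the one used in the analysis.
4. Limit the blinding sentence to these photograph-based ulcer readings, and state that first detection of ulcers by field inspection is unblinded.

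A new ulcer that the inspector neither records nor finds doubtful would still be missed, so step 4 is needed even with the extra photographs.

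If the extra photographs are not taken, state that only the area of photographed ulcers is read blind, with the date masked. State also that prevalence, and zero areas without a photograph, are unblinded, and interpret the before-after prevalence result accordingly.

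The cost is some extra tablet photographs and reading time for existing staff. At an assumed prevalence of 30%, sites ulcerated at baseline would need follow-up photographs in about 54 people at two visits, or 54 × 2 = 108 person-visits. Some of these would be photographed anyway, and doubtful lesions and new ulcers would add to the number. The fallback costs only wording.

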### Qualitative data

We will collect data on the implementation of the intervention, examining fidelity and any local adaptations. We will also examine the mechanisms of impact, through participant and facilitator perceptions of the intervention and accounts of how they have acted in response. We will explore facilitators and barriers to intervention success (or not). Finally we will examine the contextual factors (social and environmental) that shape or mediate the intervention in each cluster. These factors will be explored using the methods listed in Table 2.

**Table 2 Tab2:** Key Components of the IMPACT Process Evaluation

Component	Topic	Method(s)
Implementation	Was the intervention implemented with a high degree of fidelity?	Observations of 18 group meetings (one per cluster) – using template notes Interrogate group attendance logs and activity records (photographed monthly) in each cluster
	Which behaviour change techniques are used?	Observations of group meetings (*n* = 18)
Mechanisms	How do facilitators, group leaders and group members interpret their roles and interact with each other	Observation of group meetings (*n* = 18) Individual interviews with overall facilitator and 3 local facilitators
	To what extent is the intervention sensitive to facilitator/group leader effects?	Observation of group meetings (*n* = 18) and comparison of differences between those groups Individual interviews with overall facilitator and 3 local facilitators Group interviews with a random sample of 9 groups stratified by facilitator
	To what extent (and how) has the IMPACT intervention been effective in facilitating behaviour change amongst participants?	Observations of group meetings (*n* = 18) Group interviews (*n* = 9) stratified by facilitator Individual walking interviews with 2 randomly sampled participants (1 male, 1 female) from 9 groups using photo elicitation
	How, if at all, have self-help group meetings helped participants improve their health, social and economic wellbeing?	Exploration of lived experiences through group interviews (*n* = 9) and individual walking interviews (*n* = 18) using photo elicitation
	What are the experiences of those in the control groups?	Semi-structured individual interviews with 4–5 group members across 9 clusters
Social context (including the social environment)	How does the social context shape the intervention? What is the community perception of people who are differently abled?	Group interviews (*n* = 9) Individual interviews with influential members of the broader local community (details of whom will be derived from earlier interviews and roles/numbers may vary between clusters)
Environmental context	How does the environmental context shape the intervention?	Researcher observations from individual interviews, group interviews and walking interviews on availability of support (e.g. community health workers). Information gathering on proximity to services, water and sewage provision, location of each group, village size (population), crops grown, sources of income, distance from the nearest health facility and town/city using template.

